### Electrical cardioversion

Patients will be interviewed by telephone at 6 and 12 months to detect AF recurrences.

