**Study design:**

This study is a prospective observational study. Three separate study groups are defined: (1) cardiothoracic surgery, (2) pulmonary vein isolation and (3) electrical cardioversion. An intra-operative high-resolution epicardial (group 1) or endocardial (group 2) mapping procedure of the atria is performed to study atrial electropathology. Blood samples for Heat Shock Protein determination are obtained at baseline and during the follow-up period at 3 months (group 2), 6 months (groups 1 and 2) and 1 year (group 1 and 2). Tissue samples of the right and left atrial appendages in patients in group 1 are analysed for Heat Shock Protein levels and for tissue characteristics. Early post procedural atrial fibrillation is detected by continuous rhythm monitoring, whereas late post procedural atrial fibrillation is documented by either electrocardiogram or 24-h Holter registration.

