**Fig. 3 Fig3:**
[figure not shown]
Timecourse of the HALT & REVERSE project. A baseline blood sample (*red bar*) is obtained from all patients 1 day prior to the procedure. In the pulmonary vein isolation—and cardiac surgery group, the study procedure (*black bar* epicardial or endocardial mapping procedure) is performed during the elective therapeutic intervention (*yellow bar*) and post-procedural continuous rhythm monitoring afterwards (*green bars*). The *blue bars* indicate long term follow-up (>3 months) including a visit to the outpatient clinic with electrocardiography, blood samples and 24-h Holter recordings when indicated

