**Fig. 4 Fig4:**
[figure not shown]
Epicardial mapping scheme. *1* Left superior pulmonary vein; *2* right superior pulmonary vein; *3* left inferior pulmonary vein; *4* right inferior pulmonary vein; *5* inferior caval vein; *6* superior caval vein; *7* coronary sinus. The left and right atrium and Bachmann’s Bundle are mapped following a predefined epicardial mapping scheme along anatomical structures, by the use of an 192 polar electrode array (*green*)

After introduction cannulas of the cardiopulmonary bypass into the right atrium via the right atrial appendage (RAA) a tissue sample is obtained from the incision site in all patients. A tissue sample of the left atrial appendage (LAA) is obtained if the LAA is incised or amputated during surgery. All collected tissue samples are immediately snap-frozen in liquid nitrogen and stored at −80 °C.

After the surgical procedure, heart rhythm is continuously monitored until hospital discharge in order to detect early post-operative AF (PoAF). PoAF is defined as a complete irregular heartbeat without consistent P waves, sustaining for at least 30 s. At 6 months and 1 year after the procedure, patients visit the outpatient clinic for detection of late post-operative AF. A 12-lead electrocardiogram and a blood sample for HSP analysis are obtained. A 24-h Holter registration is performed when AF is suspected.

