### Pulmonary vein isolation

An endovascular mapping procedure is performed prior to isolation of the pulmonary veins. Atrial electropathology is studied by means of programmed electrical stimulation in the right and the left atrium, including fixed rate atrial pacing, delivery of atrial extra systoles and decremental pacing maneuvers. Recordings of the right atrium are made by a decapolar catheter at the right atrial free wall and pacing is performed from the ablation catheter, which is positioned in the RAA. Mapping in the left atrium is performed by placing a Lasso catheter at the posterior wall and a decapolar catheter in the coronary sinus, while pacing from the left atrial roofline. Subsequently, the PVI is performed according to the electrophysiologist’ choice by either radiofrequency ablation or cryoballoon ablation.

According to standard care, heart rhythm is monitored continuously until discharge. Recordings are analyzed to detect early AF episodes, sustained for at least 30 s. At 3, 6 months and 1 year after the procedure, patients visit the outpatient clinic. During these visits, 12-lead ECGs and 24-h Holter registrations are performed to detect late post procedural AF recurrences and an additional blood sample is obtained for HSP level determination.

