### Study endpoints

For all groups, endpoint of the study is reached when AF develops after cardiac surgery or recurs after ECV or PVI. The correlation between several biomarkers (HSP70, HSP27) and development or recurrences of AF is determined, but also the correlation between degree of electropathology and development or recurrences of AF. The relationship between atrial electrophysiological variables, as visualised by epicardial mapping, and structural tissue characteristics are tested. The findings will indicate whether HSP levels and/or the degree of electropathology represent a novel diagnostic tool to predict the clinical outcome of AF progression and/or recurrences.

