### Statistical analysis

The association between biomarker levels and development or recurrence of atrial fibrillation is calculated using multivariate logistic regression (for short term outcome) and cox regression models (for long-term outcome). Furthermore, Kaplan–Meier life tables are created for the three groups (cardiac surgery, PVI and ECV) and Log rank tests are used to compare the different groups.

ANOVA is utilized to compare various electrophysiological continuous parameters, for categorical parameters the Chi-square test will be used. Repeated HSP measurements are conducted by Joint modeling and mixed modeling analysis. Multiple biomarkers levels are corrected by ANOVA with Bonferoni adjustments.

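### Late AF after cardioversion is sought only by telephone, against the abstract's ECG/Holter rule, and unequal late detection undermines the log-rank comparison of the three groups

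*Protocol article*

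**What the plan says.** All in the protocol article:

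- **Abstract, Study design.** The rule for late AF names no group: "late post procedural atrial fibrillation is documented by either electrocardiogram or 24-h Holter registration".
- **Electrical cardioversion (under Study design).** The whole follow-up is one sentence: "Patients will be interviewed by telephone at 6 and 12 months to detect AF recurrences". No section gives these patients a follow-up ECG or Holter.
- **Intra-operative mapping procedure (text after Fig. 4).** At the 6-month and 1-year surgical visits, "A 12-lead electrocardiogram and a blood sample for HSP analysis are obtained", and in addition "A 24-h Holter registration is performed when AF is suspected".
- **Pulmonary vein isolation.** For the visits at 3, 6 and 12 months: "During these visits, 12-lead ECGs and 24-h Holter registrations are performed to detect late post procedural AF recurrences".
- **Fig. 3 legend.** Long-term follow-up is summarised as "including a visit to the outpatient clinic with electrocardiography, blood samples and 24-h Holter recordings when indicated", without saying which groups this covers.
- **Study endpoints.** One endpoint serves everyone: "For all groups, endpoint of the study is reached when AF develops after cardiac surgery or recurs after ECV or PVI".
- **Statistical analysis.** Long-term outcome is analysed by Cox regression. Kaplan-Meier tables are made for the surgery, PVI and ECV groups, and "Log rank tests are used to compare the different groups".

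**The concern.** Two things follow from these passages.

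First, the article contradicts itself on how the endpoint is established in ECV. The abstract promises a recorded rhythm, and the ECV section provides an interview. An interview can pick up AF that the patient felt or that someone else diagnosed. It cannot find asymptomatic AF that nobody recorded. Unless a record is obtained, the date of a recurrence is the patient's recollection or simply the interval between calls, which is thin input for a time-to-event analysis.

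Second, the three groups share an endpoint but are examined for it with very different intensity. A log-rank test across them compares the time to *detected* AF. If one group is looked at less closely, its curve stays higher for that reason alone, and a significant result could be read as a difference between patient groups when it is partly or wholly a difference in follow-up.

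**Working it through.** The plan gives no figure on detection, so there is nothing to reproduce. The first step sets the passages side by side, and the later steps are illustrations.

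**Step 1. Late follow-up by group**

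| Group | Scheduled late contacts | ECG | 24-h Holter | Meets the abstract's ECG-or-Holter rule? |
|---|---|---|---|---|
| Surgery | 6, 12 months | at each visit | only on suspicion | yes, through the ECG |
| PVI | 3, 6, 12 months | at each visit | at each visit (section text); as indicated (Fig. 3 legend) | yes |
| ECV | 6, 12 months, by telephone | none stated | none stated | **no** |

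The contradiction with the abstract is confined to ECV. The first scheduled late look is at 3 months in PVI and at 6 months in the other two groups, so the curves can separate between those times through the schedule alone.

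**Step 2. What unequal detection can do to the group comparison**

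Inputs from the article: 100 patients per group (Study population); expected 1-year recurrence of 45% after PVI and 25–40% after ECV (Sample size calculation). Assumptions: the true 1-year AF rate p is equal in two groups; one of them detects only a share s of what the other detects; there are no false positives; the test is two-sided at 0.05. A two-proportion test stands in for a pairwise log-rank test.

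With q = s·p and p̄ = (p + q)/2:

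- se₀ = √[2·p̄(1 − p̄)/100]
- se₁ = √[(p(1 − p) + q(1 − q))/100]
- chance of a significant difference = Φ[(p − q − 1.96·se₀)/se₁]

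For p = 0.45 and s = 0.7:

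- q = 0.315 and p̄ = 0.3825
- se₀ = √(2 × 0.3825 × 0.6175/100) = 0.0687
- se₁ = √((0.2475 + 0.2158)/100) = 0.0681
- (0.135 − 1.96 × 0.0687)/0.0681 ≈ 0.00, so the chance is Φ(0.00) ≈ 0.50

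| s | Observed rate if true rate is 45% | Chance of false difference, p = 45% | p = 40% | p = 25% |
|---|---|---|---|---|
| 0.9 | 40.5% | 0.09 | 0.08 | 0.06 |
| 0.8 | 36.0% | 0.25 | 0.22 | 0.13 |
| 0.7 | 31.5% | 0.50 | 0.43 | 0.25 |
| 0.6 | 27.0% | 0.76 | 0.68 | 0.42 |
| 0.5 | 22.5% | 0.93 | 0.88 | 0.62 |

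The formula counts only results in the direction of the under-detecting group. The opposite direction adds less than one percentage point at every value shown. With equal detection (s = 1) the two-sided rate is the nominal 0.05.

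**Step 3. Within ECV, illustration only**

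Assume 100 patients split at the median HSP level (50 and 50), with true recurrence of 50% and 30%. The same formula with n = 50 per half gives power of 0.53 with full detection, 0.40 at s = 0.8 (observed 40% and 24%) and 0.29 at s = 0.6 (observed 30% and 18%). The split and the rates are invented. The calculation shows only the direction of the effect.

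**The case against.** The best defence is that this is a condensed article about an observational pilot. Telephone follow-up is a reasonable feasibility choice, and the full protocol may require records to confirm what patients report. ECV patients enter with symptomatic AF, and an interview can bring out recurrences already diagnosed elsewhere, so its sensitivity may be fairly high. At 0.9 the illustration gives a false-difference rate of only 6–9%. The groups also differ in kind (new AF after surgery, recurrence after PVI or ECV), so few readers would interpret a log-rank difference causally.

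Much of this stands. Calling the ECV endpoint unverified would be an inference from silence; what can be said is that no verification is stated. The sensitivity is unknown. But condensation does not explain the conflict: the article states the ECV method, and its abstract states a different one. The group comparison is also in the plan, whatever weight readers give it.

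Several stronger readings are tempting and are not supported:

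- *Surgery also contradicts the abstract.* It does not. The abstract accepts ECG or Holter, and every surgical patient has an ECG at both visits.
- *Silent AF is missed in two of three groups.* This is a matter of degree. Surgical ECGs can catch silent AF present at the visit, early post-operative AF is under continuous monitoring until discharge, and three 24-h Holters after PVI also miss some intermittent AF.
- *Suspicion-triggered Holter biases the HSP association in surgery.* Suspicion may well be higher in patients with an AF history, but the article does not define the trigger and shows no link to HSP level.
- *The 25–40% ECV rate cannot be expected from telephone reports.* That depends on how the cited studies followed their patients, which is not shown, and the rate enters no formula.
- *The study loses a stated power.* It claims none. The 0.95 refers to sizing a later study.
- *PVI patients do not routinely get Holter.* The Fig. 3 legend is shared and may cover more than one schedule. It is a wording conflict only.

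**Conclusion.** The point holds in a limited form. It is certain from the text that ECV follow-up by telephone conflicts with the abstract's rule for documenting late AF, and that the three groups are followed with unequal intensity while sharing one endpoint and one log-rank comparison. Unequal detection can by itself produce a significant group difference. The chance is about 9%, 50% and 93% at relative sensitivities of 0.9, 0.7 and 0.5 with a true rate of 45%, and 6%, 25% and 62% with a true rate of 25%. These figures rest on assumed sensitivities, equal true rates, no false positives and a binary stand-in for the log-rank test. They show what could happen and do not estimate what will. Weakening of the HSP association within ECV is plausible, but its size cannot be derived from the article. The matter is worth correcting because the correction is cheap. It does not invalidate the study.

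**What to change.** 1. At the two planned ECV calls, ask for existing ECGs, rhythm strips and cardioversion records from the hospital or general practitioner. Classify each recurrence as ECG-documented, with its date, or patient-reported only, and analyse with and without the unconfirmed reports.
2. In surgery, analyse late AF with and without findings from Holters triggered by suspicion.
3. Drop the log-rank comparison between surgery, PVI and ECV, or label it descriptive. State that AF rates are not comparable across the groups because detection differs.
4. Correct the abstract sentence for ECV, and reconcile the Fig. 3 legend with the PVI section on Holter.
5. State as a limitation that silent AF nobody recorded is not detected in ECV. Record retrieval confirms and dates reported AF but cannot recover this.

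The cost is record requests attached to two existing contacts, two extra analyses and some rewording. No new procedure is added. Some reported recurrences will stay unconfirmed, which is why they are kept as a separate category.

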### Tissue analysis

All obtained blood samples and atrial tissue samples are stored at −80 °C until analysis. All samples are tested for HSP biomarkers, including HSP70 and HSP27. Biomarker levels are determined by commercially available ELISA’s and Western blot analysis.

## Main study parameters

### Intra-operative mapping

Custom-made software used for off-line analysis of the recordings have previously been described in detail [32–34]. Local activation times of the unipolar atrial potentials are automatically detected in order to reconstruct color-coded activation-, conduction block-, breakthrough-, voltage- and wavemaps during sinus rhythm and AF [32–34]. An example of an activation and wavemap constructed during AF is given in Fig. 5. The maps are used to quantify electrophysiological variables. These variables are correlated with the pre-operative HSP level and development of post-operative AF.

**Fig. 5 Fig5:**
[figure not shown]
Epicardial high-resolution mapping of the atria. Atrial electrograms recorded during sinus rhythm (SR), atrial pacing (P) and (electrically induced) atrial fibrillation (AF) obtained during the epicardial mapping procedure are shown in the *upper panel*. The *left lower panel* shows an example of an activation map during electrically induced AF of the right atrium in a patient undergoing coronary artery bypass grafting without a history of AF. Isochrones are drawn at 5 ms, areas of conduction block are indicated by *black bars*, the origin of peripheral and epicardial breakthrough waves by respectively *grey dots* and *white asterisks*. The *arrows* indicate main activation direction. Corresponding wavemap is displayed in the *right lower panel*. The wavemap shows the different types of fibrillation waves entering the mapping area from various directions. These maps are used to determine the incidence of e.g. conduction block and epicardial breakthrough

### Pulmonary vein isolation

The degree of fractionated electrograms obtained from multiple sites in the right and left atrium are studied for fractionation and cycle length variation. HSP levels prior to PVI are correlated with the development of AF recurrence.

### Electrical cardioversion

Correlation between HSP levels prior to cardioversion and successful restoration of sinus rhythm and AF recurrences is determined.

### Study endpoints

For all groups, endpoint of the study is reached when AF develops after cardiac surgery or recurs after ECV or PVI. The correlation between several biomarkers (HSP70, HSP27) and development or recurrences of AF is determined, but also the correlation between degree of electropathology and development or recurrences of AF. The relationship between atrial electrophysiological variables, as visualised by epicardial mapping, and structural tissue characteristics are tested. The findings will indicate whether HSP levels and/or the degree of electropathology represent a novel diagnostic tool to predict the clinical outcome of AF progression and/or recurrences.

### Statistical analysis

The association between biomarker levels and development or recurrence of atrial fibrillation is calculated using multivariate logistic regression (for short term outcome) and cox regression models (for long-term outcome). Furthermore, Kaplan–Meier life tables are created for the three groups (cardiac surgery, PVI and ECV) and Log rank tests are used to compare the different groups.

ANOVA is utilized to compare various electrophysiological continuous parameters, for categorical parameters the Chi-square test will be used. Repeated HSP measurements are conducted by Joint modeling and mixed modeling analysis. Multiple biomarkers levels are corrected by ANOVA with Bonferoni adjustments.

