### Study objectives

The primary study objectives are to test the correlation between atrial electropathology as visualised by high-resolution epicardial mapping or endovascular mapping, HSP levels, atrial tissue characteristics and clinical characteristics in patients undergoing either open chest cardiac surgery, PVI or ECV. Secondly, the correlation between HSP levels and development or recurrence of AF in patients undergoing cardiothoracic surgery, PVI or ECV is tested.

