### Study population

For the HALT & REVERSE project, three separate study groups are defined, consisting of patients scheduled for (1) cardiothoracic surgery, (2) PVI and (3) ECV for symptomatic AF. Each group contains 100 consecutive patients. Patients are recruited at the Department of Cardiothoracic Surgery or at the Department of Cardiology at the Erasmus Medical Center, Rotterdam, The Netherlands. Prior to enrolling in the study, each patient is provided an oral and a written explanation of the study procedure. Written informed consent is obtained from all patients.

Blood samples for baseline HSP level determination taken from all patients prior to the scheduled intervention (surgery, PVI or ECV) (Fig. 3). Patient characteristics (e.g. age, medical history, cardiovascular risk factors) are obtained from the patient’s file.

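### The planned log-rank test between surgery, PVI and ECV serves no stated objective, and neither a significant nor a null result could be interpreted

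*Protocol article*

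**What the plan says.** The Statistical analysis section has two separate parts that bear on time to AF.

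- **HSP and AF.** "The association between biomarker levels and development or recurrence of atrial fibrillation is calculated using multivariate logistic regression" for short-term outcome, and Cox regression for long-term outcome.
- **Curves and log-rank.** Kaplan–Meier tables are "created for the three groups (cardiac surgery, PVI and ECV) and Log rank tests are used to compare the different groups". No HSP strata are mentioned, so the groups compared are the three procedures.

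The objective that the AF outcome serves is in Study objectives: "the correlation between HSP levels and development or recurrence of AF in patients undergoing cardiothoracic surgery, PVI or ECV is tested". Study population states that "three separate study groups are defined, consisting of patients scheduled for (1) cardiothoracic surgery, (2) PVI and (3) ECV for symptomatic AF", and "Each group contains 100 consecutive patients". Study endpoints defines the event: "For all groups, endpoint of the study is reached when AF develops after cardiac surgery or recurs after ECV or PVI".

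**The concern.** A log-rank test between groups is informative when the groups share an event, that event is ascertained comparably, and the contrast answers a question of the study. None of these conditions is met here. Group membership is fully confounded with case mix, with the meaning of the event and with the intensity of rhythm surveillance. Each procedure has its own detection schedule, so covariate adjustment cannot separate detection from procedure.

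What is at stake is a published p-value that invites the reading that one procedure leaves more AF than another, which the design cannot support. A null result would be equally uninformative, because differences in incidence and in detection could offset each other.

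**Working it through.** **1. Is the comparison asked for?** Study objectives lists associations among electropathology, HSP levels, tissue and clinical characteristics, and between HSP and AF. Study endpoints adds electropathology against AF. Neither section contrasts the procedures.

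**2. Are the groups comparable?**

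| | Surgery | PVI | ECV |
|---|---|---|---|
| Population (Inclusion criteria) | Structural heart disease, prior AF or not | All have AF, paroxysmal to long-standing persistent | All have symptomatic AF |
| Event (Study endpoints) | AF develops | AF recurs | AF recurs |
| Early detection | Continuous monitoring to discharge | Continuous monitoring to discharge | None given in the ECV section |
| Late detection | ECG at 6 and 12 months, Holter only on suspicion | ECG and Holter at 3, 6 and 12 months | Telephone at 6 and 12 months |

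The detection rows come from Intra-operative mapping procedure, Pulmonary vein isolation ("During these visits, 12-lead ECGs and 24-h Holter registrations are performed to detect late post procedural AF recurrences") and Electrical cardioversion ("Patients will be interviewed by telephone at 6 and 12 months to detect AF recurrences"). The abstract says, without restricting it to particular groups, that late AF is documented by ECG or Holter. The ECV section and the abstract therefore do not agree on how ECV recurrences are established.

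**3. How might the test behave?** The article gives no figure for the log-rank test, so there is nothing to reproduce. As a crude proxy, take a chi-square test (2 df) on AF yes/no with 100 per group. The rates come from Sample size calculation: 25% surgery, 45% PVI, 25–40% ECV. With E the mean count, X² = Σ(O−E)²/E + Σ(O−E)²/(100−E).

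- 25/45/25: E = 31.67, Σ(O−E)² = 266.67, X² = 8.42 + 3.90 = 12.32, p = 0.002.
- 25/45/32: E = 34, Σ(O−E)² = 206, X² = 6.06 + 3.12 = 9.18, p = 0.010.
- 25/45/40: E = 36.67, Σ(O−E)² = 216.67, X² = 5.91 + 3.42 = 9.33, p = 0.009.

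A simulated three-group log-rank test with no HSP effect (1,000 runs each, rates treated as 1-year risks) rejects in about 88%, 78% and 80% of runs at ECV rates of 25%, 32.5% and 40%.

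**4. How fragile is that?** The 25% surgical figure is for early postoperative AF, while the other two are 1-year rates. The surgical endpoint also takes in late AF, so its 1-year rate may be higher. Keep PVI at 45% and ECV at 40%, and vary the surgical rate (values above 25% are assumptions):

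| Surgery | Chi-square p at these counts | Simulated chi-square rejection |
|---|---|---|
| 25% | 0.009 | 80% |
| 30% | 0.085 | 51% |
| 35% | 0.35 | 24% |
| 40% | 0.71 | about 10% |

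For 35/45/40: E = 40, Σ(O−E)² = 50, X² = 1.25 + 0.83 = 2.08. With ECV at 25% instead, 35/45/25 still rejects in 77% of runs.

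**5. Can detection alone produce a difference?** Here the true 1-year incidence is the same in all groups. All sensitivities are assumptions, in the order surgery/PVI/ECV.

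- Log-rank on the article's visit times, true incidence 45%: about 7% rejection if every event is found; 76%, 91% and 86% for 0.8/1/0.6, 0.7/1/0.5 and 0.6/1/0.6.
- Chi-square, true incidence 40%: about 42% for 0.6/0.8/0.5 and 71% for 0.5/0.8/0.4, but 23% for 0.8/0.8/0.6 and 9% for 0.8/0.8/0.7.

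Unequal detection can produce rejection, but by how much depends on sensitivities that the article does not give.

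**The case against.** The strongest reply is that the HSP question does not rest on this test. The sentence just before it plans logistic and Cox regression of AF on biomarker levels, and joint modelling is planned for repeated HSP measurements. That stands. A reader might infer that the between-procedure test is the only survival analysis planned, or that time to AF is never related to HSP. The article does not support that: Cox regression on biomarker levels is exactly such an analysis.

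A reader might also infer from the planning rates that a significant result is almost certain. That is not supported either. It depends on treating an early postoperative rate as a 1-year risk, and on assumed sensitivities where detection is invoked.

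Two further replies carry some weight. The study is described as a pilot, and no stated conclusion depends on this test. HSP cut-points and stratified curves can also reasonably be left to a fuller document, so the absence of HSP curves is not itself an error.

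What does not stand is reading the compared groups as HSP groups, since the text names only the procedures. Nor is this merely descriptive, since a significance test is specified.

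**Conclusion.** The point holds for the Kaplan–Meier/log-rank sentence only. The planned test contrasts three non-randomised groups that differ in population, event and detection. It answers no objective and carries no information on HSP. This conclusion rests on the text alone and needs none of the numerical assumptions.

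The numbers are illustration. The proxy p-value runs from about 0.002 to 0.010 at the planning rates and rises to about 0.35 at an assumed 35% surgical rate with ECV at 40%. The result could thus go either way, and neither outcome would be interpretable. Severity is minor to moderate: no HSP estimate changes if the test is run, but its p-value could mislead.

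**What to change.** - Delete the between-procedure log-rank test, or show the three curves descriptively without a test and state the differences in population, event and detection beside them.
- Within each procedure group, draw Kaplan–Meier curves by prespecified baseline HSP70 and HSP27 level, as a supplement to Cox regression on continuous HSP and not a replacement. A split loses information. By Schoenfeld's formula with a median split and two-sided 0.05, power = Φ(√(d/4)·ln HR − 1.96). At an assumed hazard ratio of 2 this is 0.41 with 25 events, 0.59 with 40 and 0.64 with 45.
- If an HSP effect pooled over procedures is wanted, stratify the Cox model by group.
- Reconcile the abstract and the ECV section on how late AF is documented in that group.

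The cost is analysis and reporting wording only, with no new data or patients. What is lost is a between-procedure p-value that no objective needs.

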Recently it was demonstrated that derailment of cardiomyocyte proteostasis, underlies AF progression and recurrences [12–15]. Cells, including cardiomyocytes, depend for proper functioning on the maintenance of proteostasis: the balance in protein synthesis, folding, assembling, trafficking, and clearance [16, 17] (Fig. 1). Chaperones, mainly consisting of Heat Shock Proteins (HSPs), assist in the maintenance of proteostasis [17–19]. Upon acute stress e.g. in paroxysmal AF, HSPs are upregulated [20]. The progressive nature of AF lies in the gradual, often age-related, exhaustion of the HSP levels and subsequent derailment of proteostasis, resulting in structural remodeling and contractile dysfunction of cardiomyocytes (Fig. 2). Therefore, compounds that boost HSP expression, such as geranylgeranylacetone (GGA) and GGA derivatives [21, 22], are of clinical interest. Indeed, HSPs boosting, via Heat Shock Factor-1 activation, protected against derailment of proteostasis and AF progression and recurrences in several experimental AF models, including tachypaced cardiomyocytes [23], *Drosophilas* [15] and canine models [24].

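### The planned joint model of repeated HSP can read an effect of AF on HSP as prediction of AF, because every follow-up sample is drawn at the visit that looks for AF

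*Protocol article*

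**What the plan says.** The Statistical analysis section relates biomarker levels to AF by logistic regression for short-term outcome and Cox regression for long-term outcome. It then adds: "Repeated HSP measurements are conducted by Joint modeling and mixed modeling analysis". It does not name the groups, or the event to which HSP is joined.

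The sampling schedule is fixed elsewhere in the article:

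- **All groups:** one baseline sample before the procedure (Study population).
- **Follow-up samples:** "during the follow-up period at 3 months (group 2), 6 months (groups 1 and 2) and 1 year (group 1 and 2" (Abstract, Study design).
- **Surgery:** "At 6 months and 1 year after the procedure, patients visit the outpatient clinic for detection of late post-operative AF". At those visits, "A 12-lead electrocardiogram and a blood sample for HSP analysis are obtained" (Intra-operative mapping procedure, text after Fig. 4). Early AF is found by continuous monitoring up to discharge.
- **PVI:** ECG and Holter are done at 3, 6 and 12 months to find late recurrence, and at the same visits "an additional blood sample is obtained for HSP level determination" (Pulmonary vein isolation).
- **ECV:** "Patients will be interviewed by telephone at 6 and 12 months to detect AF recurrences". No follow-up sample is listed.

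Study endpoints makes the first AF after the procedure the endpoint. On the biology, Background states: "Upon acute stress e.g. in paroxysmal AF, HSPs are upregulated". The Fig. 2 caption adds that HSP becomes exhausted as AF lasts longer.

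**The concern.** A joint model ties the path of a marker up to the event to the hazard of that event. It needs marker values that belong to the time before the event. Here the blood sample and the AF check share a visit. When AF is found at a visit, it may have begun at any time since the previous one, so the sample drawn that day may already carry its effect. If the event is dated at that visit, the model accepts the sample as the last value before the event. Patients still AF-free at the same visit contribute samples without that effect, and the contrast feeds the association parameter.

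On the protocol's own account the distortion could go either way. A rise with paroxysmal AF would make high HSP look predictive, and exhaustion with lasting AF would make low HSP look predictive. The study aims at a diagnostic tool that predicts AF, so mistaking a consequence for a predictor touches that aim directly.

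**Working it through.** The plan gives no figure on this point to reproduce. The check counts how many repeat samples can precede each event.

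**Step 1. Largest possible number of pre-event repeats, from the schedule alone**

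| Event | Samples from earlier follow-up visits |
|---|---|
| Surgery, AF before discharge | 0 |
| Surgery, found by the 6-month visit | 0 |
| Surgery, found after 6 and by 12 months | 1 |
| PVI, found by the 3-month visit | 0 |
| PVI, found after 3 and by 6 months | 1 |
| PVI, found after 6 and by 12 months | 2 |
| ECV, any | 0 (no repeats planned) |

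**Step 2. Inputs for the share of late events with none**

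- From the article: 100 patients per group; 45% recurrence 1 year after PVI, so 100 × 0.45 = 45 events.
- Assumed, because the article does not give them: the timing of PVI recurrence within the year (Weibull, shape *k* from 1, constant hazard, to 0.35, strongly front-loaded), and the number *L* of late surgical AF events (0, 10 or 20, with the same shape).
- All 45 PVI recurrences are counted as late. The 25 expected early surgical events (25% of 100) are left out, since the plan sends short-term outcome to logistic regression.

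**Step 3. Formula**

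With 1-year risk *p*, H = −ln(1 − p) and *t* in years, expected events by *t* per 100 patients = 100 × [1 − exp(−H·t^k)]. Events with no earlier repeat are those by t = 0.25 in PVI and by t = 0.5 in surgery. The share is their sum divided by 45 + L.

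**Step 4. Constant hazard (k = 1)**

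- PVI: H = −ln(0.55) = 0.598. By 3 months, 100 × [1 − exp(−0.598 × 0.25)] = 13.9 events. Between 3 and 6 months 12.0, and between 6 and 12 months 19.2. So about 14, 12 and 19 of 45 have zero, one and two earlier repeats.
- PVI alone: 13.9/45 = 31% with none.
- Adding surgery with L = 20: H = −ln(0.80) = 0.223; by 6 months, 100 × [1 − exp(−0.223 × 0.5)] = 10.6. The share is (13.9 + 10.6)/65 = 38%.

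**Step 5. Range over the assumptions**

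| Shape k | PVI events by 3 months, of 45 | Share with none, L = 0 | L = 10 | L = 20 |
|---|---|---|---|---|
| 1 | 13.9 | 31% | 35% | 38% |
| 0.75 | 19.1 | 42% | 46% | 48% |
| 0.5 | 25.8 | 57% | 60% | 62% |
| 0.35 | 30.8 | 68% | 70% | 72% |

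**Step 6. What the detecting-visit sample adds**

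For every event in the zero-repeat rows of surgery and PVI found at a visit, the only follow-up value available by the detection date is the one drawn at detection. In those patients any apparent change from baseline comes wholly from a sample that AF may have altered.

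**The case against.** The strongest reply is that one sentence in a condensed article does not say that samples at or after detection will be used as predictors, and that the full plan may settle this. A joint model also does not need a repeat before every event: AF-free patients contribute whole trajectories, and patients with baseline only still contribute. The prediction analyses named under Main study parameters use HSP measured before surgery, PVI or cardioversion.

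Much of this stands, and it rules out several stronger readings that a reader might infer:

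- **That ECV, with one sample, contradicts the plan.** It does not. The sentence concerns repeated measurements, which exist only in surgery and PVI.
- **That most events lack a pre-event repeat.** Over all three groups the stated rates do give 25 + 25 = 50 of 95 up to 25 + 40 = 65 of 110 (53-59%), even with no PVI event by 3 months and no late surgical AF. But that counts ECV events and early surgical AF, which the joint model would not naturally use. Among late events in surgery and PVI, more than half lack one only if recurrence is strongly front-loaded.
- **That the main prediction results are biased.** Those using pre-procedure HSP are not.
- **That the joint model must be dropped.** That is a trade-off, not a correction.

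What the reply does not remove is the coincidence of sample and detection. It comes from the stated schedule together with the stated method, and an ordinary joint model dated at the detecting visit takes in the affected sample by default.

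**Conclusion.** The concern holds for follow-up HSP in the surgery and PVI groups. Sampling at the detecting visit, an endpoint of first AF, and the protocol's own statement that AF alters HSP together allow reverse causation into the joint model's association parameter. The size of the bias cannot be computed, because the article gives neither the effect of AF on HSP nor the timing of AF.

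The sparseness can be bounded. No late surgical event has more than one pre-event repeat, and no PVI event more than two; this rests on the schedule alone. The share of late events with none, about 31-38% at constant hazard and 57-72% at shapes 0.5 to 0.35, rests on assumed timing and on 0 to 20 late surgical events. The point deserves a change in the analysis wording, and it leaves the baseline-HSP analyses as they are.

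**What to change.** Amend the sentence on repeated HSP as follows:

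1. Limit joint modelling to the surgery and PVI groups and to late AF.
2. Let only samples from visits before the detecting visit enter as predictors, and treat visit-detected AF as interval-censored between the last AF-free visit and the detecting visit.
3. Alternatively, use a landmark analysis in patients still AF-free: HSP at 3 months in PVI, or at 6 months in surgery and PVI, against AF detected later.
4. Use samples taken at or after detection only in the mixed model, with HSP as the outcome and AF status as a time-varying covariate.

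No new data are needed. The cost is fewer usable events and wider intervals for the follow-up HSP association. In PVI, a 3-month landmark leaves 45 − 13.9 = about 31 events at constant hazard and 45 − 30.8 = about 14 at shape 0.35. In surgery, a 6-month landmark leaves 20 − 10.6 = about 9 events at constant hazard even with 20 late events assumed. One limit remains: at surgical visits a Holter is done only when AF is suspected, so AF-free there means no AF detected. The report should say so.
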